### Measurements and outcomes

2.3

#### Primary objectives

2.3.1

To evaluate the occurrence of new CCM-related events, which are defined as intracerebral hemorrhage (ICH) or focal neurological deficits (FNDs). FNDs will be assessed by treating clinicians (neurologist or neurosurgeon) based on clinical and neuroradiological evaluation (cerebral CT or cerebral MRI).

#### Secondary objectives

2.3.2

To evaluate the new occurrence of other CCM-related clinical events, including seizures and recurrent headaches. Seizures, an important aspect of fCCMs, are assessed as a secondary endpoint rather than a primary endpoint, as their onset may be influenced by anti-convulsant therapy.To identify MRI biomarkers of disease severity and disease progression, including the number of CCM lesions, size of CCMs, signal of CCM lesions according to the Zabramski classification, lesion location, size modifications, signs of new bleeding, and the number of *de novo* CCM lesions at 12 and 24 months.To identify circulating biomarkers related to disease activity in fCCM subjects.To evaluate global cognitive function, disability, and health-related quality of life of fCCM patients.

#### Event adjudication

2.3.3

A Clinical Event Committee will be established to assess all outcome events. Once an endpoint event (ICH or FND) is reported, the Study Secretariat will collect the clinical documentation and share it with independent experts to centrally verify the event. The independent Clinical Event Committee will oversee the adjudication of all primary events in accordance with current guidelines (5).

#### Data management

2.3.4

Each participant will be assigned a unique code at the time of enrollment. Data de-identification will occur in such a way that individuals accessing the database will not be able to trace back to the identities of the subjects in any way. Only local researchers will be able to trace back to the identities of the enrolled subjects.

The data required for the study will be recorded in a dedicated eCRF within a Data Management System validated according to national regulations, provided by Institute for Pharmacological Research Mario Negri IRCCS. The platform used will be Research Electronic Data Capture (REDCap). In this study, REDCap will provide:

user-level identification with specific restrictions based on study roles,real-time data validation and integrity control,patient de-identification prior to data export, andcentralized data storage with daily backups on a secure server within the IRFMN infrastructure.

#### Sample size calculation

2.3.5

The primary endpoint, the new occurrence of CCM-related clinical events, defined as ICH and FNDs, excluding seizures, is expected in approximately 5.6% of the population based on the Treat_CCM trial (1). Assuming that 5.6% of subjects in the CCM_Italia cohort will develop a CCM-related clinical event, at least 100 patients (including a dropout of 8%) are needed to estimate this proportion with 95% confidence and 4.7% absolute precision.

According to the Treat_CCM study, 55% of fCCM patients are expected to experience increased disease activity. Dividing the population by the median level of a biomarker or imaging marker of interest (resulting in 2 groups of 50 individuals) would provide us a statistically significant result if the HR of this biomarker is at least 2.15 (power 80%, *α* = 0.05) (6, 7).

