**Methods:**

Pediatric and adult fCCM patients, whether symptomatic or asymptomatic, will be enrolled and followed annually over a 2-year period. Participants will undergo clinical assessments, blood sampling, and 3 T brain MRI scans at baseline, 12 months, and 24 months. The primary outcome is the new occurrence of symptomatic ICH or FNDs attributable to CCMs over 24 months. Patient characteristics will be assessed for the primary and secondary endpoints and illustrated using Kaplan–Meier curves and Cox proportional hazard regressions. This trial is registered with ClinicalTrials.gov, NCT06983132 and is currently recruiting participants.

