##### Primary endpoint

2.3.6.1

Patient characteristics will be compared using descriptive analyses to compare patients who reach the primary endpoint—the new occurrence of CCM-related clinical events, defined as ICH and FNDs, excluding seizures—to those who do not. The Kaplan–Meier curves will be constructed to assess the onset of the primary endpoint over time.

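### The stated 4.7-point precision at 95% confidence is a normal-approximation half-width on about 5 events and is slightly optimistic; the abstract's Cox regression for the primary endpoint does not match the methods

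*Protocol article*

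**What the plan says.** Section 2.3.5 (Sample size calculation) starts from this premise: "Assuming that 5.6% of subjects in the CCM_Italia cohort will develop a CCM-related clinical event". It concludes that "at least 100 patients (including a dropout of 8%) are needed to estimate this proportion with 95% confidence and 4.7% absolute precision". No interval method is named there or in section 2.3.6.1.

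The endpoint is defined over two years in the abstract: "The primary outcome is the new occurrence of symptomatic ICH or FNDs attributable to CCMs over 24 months". The abstract also says that patient characteristics will be assessed for the primary and the secondary endpoints and "illustrated using Kaplan–Meier curves and Cox proportional hazard regressions".

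Section 2.3.6.1 (Primary endpoint) is narrower: "Patient characteristics will be compared using descriptive analyses to compare patients who reach the primary endpoint" with those who do not, plus Kaplan–Meier curves. It names no Cox model. The only hazard-ratio calculation, in section 2.3.5, is HR 2.15 at 80% power for a median split. It rests on the 55% of patients expected to show disease activity, not on the 5.6% expected to have a primary event.

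**The concern.** A proportion near 5% in fewer than 100 patients rests on a handful of events. There the normal approximation gives an interval that is too short and wrongly symmetric, so a precision figure taken from it may not carry its stated confidence. The direction matters for a natural-history cohort: an upper limit that is too low understates how frequent hemorrhage or focal deficit could be.

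The same event count limits any regression on the primary endpoint. A reader of the abstract could expect hazard ratios for ICH or FND, and could take the 80% power statement to cover them.

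**Working it through.** **Inputs (section 2.3.5).** p = 0.056; 95% two-sided confidence, z = 1.96; precision d = 0.047; 100 enrolled; 8% dropout. For the power check: HR 2.15, α = 0.05, 80% power, median split, 55% active.

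**1. Reproduce the plan's figure.**
- n = z² p(1 − p)/d² = 1.96² × 0.056 × 0.944 / 0.047² = 91.9, so 92 evaluable.
- 92 / 0.92 = 100 enrolled, as stated.
- Half-width at n = 92: 1.96 × √(0.056 × 0.944 / 92) = 4.698 points, as stated.
- Expected events: 92 × 0.056 = 5.2 (5.6 with no dropout).

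**2. Coverage of that interval.** Sum the binomial probabilities of every event count whose Wald interval contains the true rate.
- n = 92, p = 5.6%: 88.9%.
- The upper limit lies below 5.6% whenever 2 or fewer events occur (at 2/92 it is 5.15%). The probability is 10.6%, against a nominal 2.5%.
- The lower limit lies above 5.6% only from 12 events up. The probability is 0.5%.
- n = 100, p = 5.6%: 91.3%.
- n = 92, p from 4% to 8% on a fine grid: 85.1% to 94.6%. Coverage is jagged because counts are discrete, but it stays below 95% throughout.

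**3. Intervals that hold their level better, n = 92.**

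| Method | Coverage at 5.6% | Expected half-width | 95% CI for 5/92 (5.4%) | Half-width at 5/92 | Upper arm at 5/92 |
|---|---|---|---|---|---|
| Wald | 88.9% | 4.6 points | 0.8% to 10.1% | 4.6 points | 4.6 points |
| Wilson | 96.2% | 4.8 points | 2.3% to 12.1% | 4.9 points | 6.7 points |
| Exact (Clopper–Pearson) | 98.1% | 5.2 points | 1.8% to 12.2% | 5.2 points | 6.8 points |

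The half-width grows by only a few tenths of a point. The larger change is at the upper end, where the limit moves from about 10% to about 12%.

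**4. Cox regression on the primary endpoint.** With a median split and D events, the Schoenfeld approximation gives the HR detectable at 80% power as exp[(1.96 + 0.84) / √(D/4)].
- D = 5.15: exp(2.80 / 1.135) = about 12.
- D = 5.6 (no dropout): 10.7.
- Power for HR 2.15 with D = 5.15: about 14%.
- Events needed for HR 2.15 at 80% power: 4 × 2.80² / (ln 2.15)² = 54. Disease activity is expected to supply about 55, which gives 81% power. The stated 2.15 therefore fits disease activity, and the primary endpoint supplies about a tenth of the events it needs.

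**The case against.** The other side has several good points.

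- **A reader might infer that the sample size is miscalculated.** It is not. N = 100 follows exactly from the stated inputs by a standard planning formula.
- **A reader might infer that the sponsor will publish an interval with 89% coverage.** The article does not say so. Planning with a normal approximation does not commit the analysis to Wald limits, and the choice of interval may sit in a full protocol or analysis plan that is not shown. Even so, the statement is not rescued: if Wald limits are reported, the 95% does not hold; if exact limits are reported at 92 patients, the 4.7 points does not.
- **The gap is small.** Wilson adds about 0.1 to 0.2 points. The 5.2 points comes from the exact interval, which is conservative here. Section 2.1.3 carries a discontinued patient's last status into the final analysis, and at n = 100 the Wilson half-width at 5.6% is 4.72 points, close to the stated figure. That limits the size of the point. It does not make the interval symmetric, and section 2.3.5 itself allows for 8% dropout.
- **A reader might infer that the primary proportion is never named as something to estimate.** That is weak. Section 2.3.5 says the aim is "to estimate this proportion with 95% confidence and 4.7% absolute precision", and the planned Kaplan–Meier curves yield the 24-month incidence.
- **A reader might infer that risk-factor modelling of ICH or FND is planned on 5 events.** Cox appears in one abstract sentence that covers all endpoints together. No multivariable model for the primary endpoint is described, and section 2.3.6.2 directs biomarker modelling to disease activity. What stands is the mismatch between abstract and methods.

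**Conclusion.** The concern holds in a limited form. The 95% confidence and the 4.7 points do not hold together at 92 evaluable patients and about 5.2 expected events. The interval behind the figure covers about 89% at 5.6%, and almost all of its misses are upper limits that are too low. A fair statement is about 4.9 points (Wilson) or 5.2 points (exact), with an upper arm of about 6.7 to 6.8 points if 5 of 92 have an event.

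Separately, the abstract and section 2.3.6.1 disagree on whether Cox regression is applied to the primary endpoint. On the plan's own event rate such a model could reliably detect only a hazard ratio near 12. A one-covariate model can be fitted but would say little.

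This rests on three assumptions: that the 5.6% is about right, that the 8% dropout contributes no endpoint status, and that the normal-approximation formula was used for planning. The last is inferred because it reproduces both 92 and 100. The documents show neither a wrong sample size nor a commitment to Wald limits.

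**What to change.** 1. In section 2.3.5, keep N = 100 and restate the precision as about 4.9 points (Wilson) or about 5.2 points (exact) at 92 evaluable patients. Show the asymmetric interval, for example 2.3% to 12.1% (Wilson) or 1.8% to 12.2% (exact) for 5/92.
2. In section 2.3.6.1, say that the 24-month incidence will be reported with a 95% interval that is not Wald: Wilson or exact for a simple proportion, or log-log limits for the Kaplan–Meier estimate.
3. In the abstract, remove Cox regression for the primary endpoint, or label it univariable and descriptive, so that it agrees with section 2.3.6.1.
4. In section 2.3.5, state that the HR of 2.15 at 80% power applies to disease activity only.

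The cost is wording. No patients or assessments are added, the stated precision becomes slightly less favorable, and one analysis mentioned in the abstract is dropped or relabeled.

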##### Secondary endpoint

2.3.6.2

*Clinical endpoints*: individual components of the primary endpoint, the incidence of either ICH or FNDs, and other clinical secondary endpoints such as seizures, headache, or any hospitalization, will be assessed by means of descriptive analyses. In addition, the Kaplan–Meier curves will be constructed to illustrate the occurrence of clinical events over time.

*Disease activity*: In order to explore the discriminatory power of biomarkers, we will assess a secondary endpoint: disease activity. This will be defined as CCM-related adverse events or the development of at least 5 new CCM lesions during the 2 years of observation. Based on (2), we expect at least 55% of the participating fCCM patients to be classified as “active.” Patients will be divided by the median level of a biomarker or imaging marker of interest. Logistic regression analyses will be performed to identify circulating biomarkers independently associated with increased disease activity. All outcomes will be reported with 95% confidence intervals, and in the case of -omics assessments, corrections for multiple testing will be applied.

*Questionnaires*: Global cognitive function, depression, anxiety, and health-related quality of life will be assessed in adult patients at multiple time points, and any changes over time will be described and assessed using repeated measures ANOVA.

*Neuroimaging*: Different vascular lesion characteristics, as measured by MR imaging, will be assessed for the total population and by relevant characteristics:

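### The biomarker power statement (HR 2.15, 80%) is a time-to-event calculation on all 100 patients, while section 2.3.6.2 plans logistic regression and the 100 already allows for 8% dropout; the shortfall is modest

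*Protocol article*

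**What the plan says.** Section 2.3.5 (Sample size calculation) has two parts. The first sizes the cohort on the precision of the primary endpoint proportion: "at least 100 patients (including a dropout of 8%) are needed". The second is the only power statement in the article. It assumes that "55% of fCCM patients are expected to experience increased disease activity", splits the cohort at the marker median ("resulting in 2 groups of 50 individuals"), and states that this "would provide us a statistically significant result if the HR of this biomarker is at least 2.15" ("power 80%, *α* = 0.05").

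Section 2.3.6.2 (Secondary endpoint, Disease activity) takes up the same 55% and the same median split. Of disease activity it says: "This will be defined as CCM-related adverse events or the development of at least 5 new CCM lesions during the 2 years of observation". The analysis is then given: "Logistic regression analyses will be performed to identify circulating biomarkers independently associated with increased disease activity".

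A hazard model is named only in the Methods part of the abstract, which says that patient characteristics will be assessed for the primary and secondary endpoints using Kaplan–Meier "curves and Cox proportional hazard regressions". Section 2.3.6 does not mention Cox regression.

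Section 2.1.3 (Exit study criteria) adds that a discontinued patient contributes the last known status to the final analysis.

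**The concern.** The power sentence and the analysis sentence describe the same endpoint and the same split, but different models. A hazard ratio needs event times. Logistic regression uses only the two-year status and returns an odds ratio. The lesion component has no exact event time either, because new lesions are counted at the 12- and 24-month MRI.

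The two parts of section 2.3.5 also appear to use different numbers of patients: the first allows for 8% dropout within the 100, and the second uses all 100.

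At stake is the only figure in the article that tells a reader what size of biomarker effect the study can detect. Biomarker identification is a stated aim, so that figure should describe the analysis that will be run on the patients who will be available.

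**Working it through.** **Inputs.** From section 2.3.5: HR 2.15, power 80%, α 0.05, 55% active, two groups of 50, and 100 patients including 8% dropout. From section 2.3.6.2: binary status over two years, logistic regression. Assumption: α is two-sided. The article does not say so, but the two-sided formula fits the stated figure and the one-sided one does not.

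**1. Reproduce HR 2.15.** Schoenfeld's formula with 1:1 groups:

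events = 4 × (1.96 + 0.84)² / (ln 2.15)² = 53.6, so 54.

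Events available: 100 × 0.55 = 55. Power with 55 events is Φ(√55/2 × ln 2.15 − 1.96) = 81.0%, and the detectable HR is 2.13. The stated figure therefore reproduces as a time-to-event calculation on all 100. Freedman's formula needs 59 events and one-sided Schoenfeld needs 43; neither fits.

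**2. Which number does the 100 stand for?** The half-width for a proportion of 5.6% is 1.96 × √(0.056 × 0.944 / n):
- n = 92: 4.70%
- n = 100: 4.51%

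The article states 4.7%. The precision part was thus computed on 92, and the power part on 100.

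**3. The same HR formula on 92 patients.** 92 × 0.55 = 50.6 events.
- Power at HR 2.15: Φ(√50.6/2 × ln 2.15 − 1.96) = 77.7%.
- Detectable HR at 80% power: exp(2 × 2.80 / √50.6) = 2.20.

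**4. Translate HR 2.15 into two-year proportions.** Under proportional hazards, p_high = 1 − (1 − p_low)^2.15, and the two groups must average 55%. This gives p_low = 41.5% and p_high = 68.5%. The corresponding odds ratio is (0.685/0.315) / (0.415/0.585) ≈ 3.06.

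**5. Power of the binary comparison if the true HR is 2.15.** Two-proportion test with pooled variance, two-sided 0.05:

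| Analysed | Per group | Power |
|---|---|---|
| 100 | 50 | 78.1% |
| 92 | 46 | 74.6% |

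A Wald test on the log odds ratio with 46 per group gives 72.6%.

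**6. Effect that the binary comparison detects with 80% power, 55% active overall.**

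| Per group | Active, low vs high | OR (two-proportion) | OR (Wald) |
|---|---|---|---|
| 50 | 41.2% vs 68.8% | 3.14 | 3.24 |
| 46 | 40.7% vs 69.3% | 3.30 | 3.43 |

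With a continuity correction, or with the 55% placed in one group instead of overall, the range widens to 3.1–3.5 for 100 patients and 3.3–3.7 for 92.

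**7. A discrete-time alternative.** A simulated two-interval complementary log-log model (0–12 and 12–24 months, constant hazard, 92 patients) has about 76–77% power at HR 2.15 and 79% at HR 2.20. This agrees with step 3 to within about a point.

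**The case against.** The strongest reply is that no number is miscalculated and the consequences are small. HR 2.15 reproduces. The enrolment target rests on the precision of the primary endpoint, not on this sentence. The biomarker analysis is introduced as exploratory. All of that stands, and it limits the weight of the point: this is an inconsistency between two sections, not an arithmetic error.

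A reader might set HR 2.15 beside OR 3.3 and infer that the detectable effect worsens by that much. The documents do not support this. HR 2.15 at 55% active already corresponds to an OR of about 3.06, so the like-for-like comparison is 3.06 against 3.14 (100 patients) or 3.30 (92). Most of the apparent gap is a change of scale. Likewise, the binary test has only 44–47% power at an OR of 2.15, but the article says HR, so that figure describes a mislabelling and not the design.

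A reader might also infer that no hazard ratio will be estimated at all. That goes too far. The abstract's Cox regression covers secondary endpoints, and disease activity is one, although the abstract speaks of patient characteristics and section 2.3.6 does not carry the model through. The fair statement is that the article names two models and does not reconcile them.

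Finally, 92 is not certain. Section 2.1.3 carries forward the last known status of discontinued patients, so the number analysed could lie anywhere from 92 to 100. This narrows the shortfall but does not remove it: even with all 100, the binary test has 78% power at HR 2.15.

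**Conclusion.** The point holds as a mismatch of modest size. The 80% attached to HR 2.15 belongs to a time-to-event test on 100 patients with complete follow-up. It is not reached on the plan's own inputs once dropout is removed (78% on the HR scale), nor for the planned binary comparison (75% with 92 patients, 78% with 100). Against the 81% that the formula gives for 55 events, the loss is about 3 to 6 points.

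This rests on two-sided α, 55% active overall, equal groups, proportional hazards for the HR-to-OR translation, and an unadjusted comparison. Section 2.3.6.2 looks for independent associations, which implies adjusted models; adjustment would generally not make the detectable OR smaller. The sample size and the primary analysis are unaffected.

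**What to change.** In section 2.3.5, replace the hazard-ratio sentence with the effect that the planned model can detect in the patients expected to be analysed. For example: *With 92 evaluable patients (46 per group), 55% active and two-sided α of 0.05, there is 80% power to detect about 41% vs 69% active, an unadjusted OR of about 3.3 (about 3.1 if all 100 are analysed).* The word unadjusted should stay, because the figure is not for a multivariable model.

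If a time-to-event or discrete-time model is what is intended for disease activity, name it in section 2.3.6.2 in place of logistic regression and state HR about 2.2 for 92 patients.

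In either case, make the abstract and section 2.3.6 name the same model. The cost is about two sentences and a less favourable stated effect, with no extra patients or procedures.

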#### Statistical analysis

2.3.6

Baseline characteristics will be presented for the total population and by relevant variables (e.g., sex, age categories, and number of CCM lesions). Relevant patient subgroups, such as gene mutation, age groups, and presence of baseline symptoms, will be compared by descriptive univariate statistics. Prior experience of the consortium has shown that data are quite complete, and imputation for missing values was not performed.

##### Primary endpoint

2.3.6.1

Patient characteristics will be compared using descriptive analyses to compare patients who reach the primary endpoint—the new occurrence of CCM-related clinical events, defined as ICH and FNDs, excluding seizures—to those who do not. The Kaplan–Meier curves will be constructed to assess the onset of the primary endpoint over time.

##### Secondary endpoint

2.3.6.2

*Clinical endpoints*: individual components of the primary endpoint, the incidence of either ICH or FNDs, and other clinical secondary endpoints such as seizures, headache, or any hospitalization, will be assessed by means of descriptive analyses. In addition, the Kaplan–Meier curves will be constructed to illustrate the occurrence of clinical events over time.

*Disease activity*: In order to explore the discriminatory power of biomarkers, we will assess a secondary endpoint: disease activity. This will be defined as CCM-related adverse events or the development of at least 5 new CCM lesions during the 2 years of observation. Based on (2), we expect at least 55% of the participating fCCM patients to be classified as “active.” Patients will be divided by the median level of a biomarker or imaging marker of interest. Logistic regression analyses will be performed to identify circulating biomarkers independently associated with increased disease activity. All outcomes will be reported with 95% confidence intervals, and in the case of -omics assessments, corrections for multiple testing will be applied.

*Questionnaires*: Global cognitive function, depression, anxiety, and health-related quality of life will be assessed in adult patients at multiple time points, and any changes over time will be described and assessed using repeated measures ANOVA.

*Neuroimaging*: Different vascular lesion characteristics, as measured by MR imaging, will be assessed for the total population and by relevant characteristics:

CCM lesions (number).CCM new lesions (number).Location of lesions (number of CCM lesions in each of the following sites: the cerebellum, the brainstem, the basal ganglia and thalami, the right cerebral hemisphere, and the left cerebral hemisphere).Radiological characteristics (size and number of CCM lesions) classified according to Zabramski classification: type I, II, III, and IV (7). The evolution of MRI markers, such as the number of new lesions, the size modification of lesions, and the signs of *de novo* bleeding, will be described. Changes over time will be assessed by means of generalized linear models with a Poisson distribution to account for the count nature of the data. Corrections for multiple testing will be applied to account for type 1 errors across multiple MRI outcomes. The assessment of changes over time will be performed for all patients included in the cohort as a change from baseline to 2-year follow-up.

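### The disease-activity analysis divides patients at an unjustified sample median of the marker; if that split is the logistic covariate, it can cost up to about 36% of the information and understates discrimination

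*Protocol article*

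**What the plan says.** Section 2.3.6.2 (Disease activity) gives the purpose first: "In order to explore the discriminatory power of biomarkers, we will assess a secondary endpoint: disease activity". Disease activity is a yes/no outcome over two years: CCM-related adverse events or at least five new lesions. The section then states "Patients will be divided by the median level of a biomarker or imaging marker of interest", and the next sentence reads "Logistic regression analyses will be performed to identify circulating biomarkers independently associated with increased disease activity". Results are to carry 95% confidence intervals. The section does not say in which form the marker enters the model.

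Section 2.3.5 uses the same division for planning: "Dividing the population by the median level of a biomarker or imaging marker of interest (resulting in 2 groups of 50 individuals"). With "55% of fCCM patients are expected to experience increased disease activity", it claims a "statistically significant result if the HR of this biomarker is at least 2.15", at 80% power and alpha 0.05. Neither section gives a reason for choosing the median.

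**The concern.** Most of the candidate markers are measurements or counts: plasma concentrations, lesion number, lesion size. A split at the median treats a patient just above it like one in the extreme tail, and it separates two patients who lie on either side of it by a trivial amount. The cut-point also belongs to this sample. The cohort is deliberately mixed, from asymptomatic to high-risk cases, so its median need not carry over to another cohort, whereas the Discussion hopes to validate biomarkers from the earlier trial.

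The split also fits poorly with the stated purpose. An odds ratio between two halves measures association. Discrimination concerns how well the whole range of the marker ranks active above non-active patients, and a single cut blurs that ranking. At stake is power in a rare-disease cohort of about 100, and the risk that a useful marker is reported as weaker than it is.

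**Working it through.** **Inputs from the document.** N = 100, including 8% dropout (92 completers); 55% active; two halves of 50; HR 2.15; power 80%; alpha 0.05 (sidedness not stated; two-sided assumed).

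**1. The plan's own figure.** Events = 0.55 × 100 = 55. Schoenfeld, equal halves:
- events needed at HR 2.15 = 4 × (1.960 + 0.842)² / (ln 2.15)² = 54 after rounding up;
- power with 55 events = Φ(√(55 × 0.25) × ln 2.15 − 1.960) = 81.0%;
- smallest HR at 80% power = exp(2.802 / √13.75) = 2.13.

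The figure of 2.15 is therefore reproduced, and it is a median-split calculation on all 100 patients.

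**2. Information lost by the split.** Asymptotic efficiency of a median split relative to a linear term:

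| Marker and effect (assumed) | Efficiency | Loss |
|---|---|---|
| Normal, linear log-odds | 2/π = 0.637 | 36% |
| Uniform, linear log-odds | 0.75 | 25% |
| True step at the median | 1 | none |

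In the normal case, 100 patients carry the information of 100 × 0.637 ≈ 64, and 92 that of about 59.

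**3. The same loss on the hazard-ratio scale (normal marker, 55 events).**
- Continuous: detectable HR per SD = exp(2.802 / √55) = 1.46.
- Split: the means of the two halves differ by 2√(2/π) = 1.596 SD, so HR 2.13 between halves equals exp(ln 2.13 / 1.596) ≈ 1.61 per SD.

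**4. Simulated logistic regression.** N = 100, 55% active, one unadjusted marker, likelihood-ratio test, 3000 runs per setting:

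| Marker | OR per SD | Power, continuous | Power, split | AUC, continuous | AUC, split |
|---|---|---|---|---|---|
| Normal | 1.82 | 81% | 63% | 0.66 | 0.61 |
| Normal | 2.12 | 93% | 80% | 0.69 | 0.64 |
| Uniform | 1.82 | 83% | 73% | 0.66 | 0.62 |

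With 92 patients and a normal marker, power was 79% against 57% at a log odds ratio of 0.6 per SD (OR 1.82), and 88% against 69% at 0.7 (OR 2.01).

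**5. The reverse case.** With 92 patients and a true step at the median (OR 3.06), power was about 57% for the continuous term and 68% for the split. The ranking depends on the shape of the effect.

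**6. Discrimination at the plan's detection limit.** Under proportional hazards, HR 2.15 with 55% active overall means about 41.5% active in one half and 68.5% in the other. For the split marker:
- sensitivity = 0.685 / (0.685 + 0.415) = 62%;
- specificity = 0.585 / (0.585 + 0.315) = 65%;
- one-cut AUC = (0.62 + 0.65) / 2 ≈ 0.64.

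A marker that just meets the planned significance target can therefore discriminate only modestly, and its odds ratio would not show this.

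**The case against.** The strongest reply is that the document never says the split is the logistic covariate. The sentence on the split covers biomarkers and imaging markers, while the one on logistic regression covers circulating biomarkers only. The split may serve description or planning, and the form of a covariate is commonly settled in an analysis plan, which is not shown. This stands as a limit: the loss applies only if the split enters the model. It does not remove the point, because the division is a stated step of the analysis, comes directly before the regression, underlies the only power statement for markers, and is not accompanied by any mention of a continuous term.

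Three stronger readings are tempting, and the documents do not support them.
- A reader might infer that every marker is dichotomised before modelling. The text speaks of a marker of interest and leaves the model open. Some imaging features, such as Zabramski type and location, are categorical in any case.
- A reader might infer that the split cannot measure discrimination at all. It gives sensitivity, specificity and a one-cut AUC; for a graded marker that AUC is attenuated.
- A reader might infer a fixed loss of a third. The document gives neither the marker's distribution nor the shape of its effect, and under a step at the median the split is the better choice.

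That the article names no AUC, covariate list or optimism correction is not an error in itself, since a condensed article commonly leaves these to the full plan. The analysis is also exploratory and secondary.

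**Conclusion.** The point holds in conditional form. Sections 2.3.5 and 2.3.6.2 plan a division at the sample median without justifying it, in an analysis whose stated purpose is discrimination. If the division enters the logistic model, as the order of the sentences suggests, the cost for a normal marker with a linear log-odds effect is about 36% of the information. At an odds ratio of about 1.8 per SD, that takes power from roughly 80% to about 60%, and the AUC is understated by about 0.05. The normal shape and the linear effect are assumptions, the simulations are unadjusted, and 92 completers is the document's dropout allowance carried over to this endpoint. The hazard ratio of 2.15 is correctly computed for the split it assumes. The change should be made, but it does not touch the primary endpoint.

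**What to change.** In section 2.3.6.2, state that:
- continuous and count markers enter the logistic model as continuous terms, log-transformed if skewed and scaled per SD, with a check of linearity;
- the AUC with its 95% confidence interval is the measure of discrimination;
- the median split is used for display only.

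Section 2.3.5 may keep the split as its planning basis, labelled as such. If the sponsor does want the split in the model, the text should say so and justify the cut-point.

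**Cost.** No new data, visits or patients. A linear term loses some power if the true effect is a threshold at the median. A three-knot spline as the linearity check costs one extra parameter. With 0.45 × 92 ≈ 41 to 0.45 × 100 = 45 non-active patients expected, the adjustment set should stay small.
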